### Clinical data

2.10

### Process evaluation

2.11

#### Fex-Can Childhood RCT

2.11.1

Post-intervention survey

In addition to the primary and secondary outcomes, the post-intervention survey will include questions regarding adherence to the program, use of the different features of the program, and perception of change in sexual problems and/or fertility-related distress. These questions will be administered to the participants belonging to the intervention group and will encompass 13 study-specific items. Participants will also be requested to comment on the content and features of the intervention. Responses will be provided on a four-point scale ranging from “Disagree completely” to “Agree completely.” Additionally, participants will be requested to score their present levels of problems (concerning sex life or fertility-related distress) in comparison to the level before they entered the Fex-Can Childhood intervention. Responses will be given on a 7-point scale, ranging from “Much improved” to “Much worsened” with the midpoint “No change.”

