### Design

2.1

The Fex-Can Childhood project started January 2019 and is expected to run till November 2020. The Fex-Can Childhood OS will have a population-based cross-sectional design, including an age matched comparison group. The Fex-Can Childhood RCT will test the effect of the Fex-Can intervention by using an RCT with a superiority design and a 1:1 allocation ratio. The active group will receive the Fex-Can intervention for 12 weeks (either the Fex-Can Sex or the Fex-Can Fertility version of the program) and the control group will be on a wait-list. The effect of the Fex-Can intervention will be evaluated directly after end of the program (primary endpoint), and at 3-month follow-up. The control group will receive access to the intervention after the 3-month follow-up assessment. An additional follow-up assessment will be conducted at 6 months after end of the program which will be used to analyze sustainment of a potential effect for the intervention group. To achieve a deeper understanding of the participants’, use of the intervention, and of the role of the program in bringing about a possible change in the selected outcomes, a process-evaluation including survey questions and qualitative interviews will also be conducted. See Figure 1 for flow diagram of the Fex-Can Childhood RCT.

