#### Semi-structured interview

2.11.2

Semi-structured interviews will be conducted with a purposive sample of ∼30 participants in the intervention group in order to achieve a deeper understanding of the intervention usage, and the role of the program in bringing about a change in the outcomes. The interviews will be performed via telephone, shortly after completion of the intervention. Questions will explore the participants’ view of their sexual problems or fertility-related distress and if/how these problems have changed during the course of the intervention. Participants will also be asked to describe their experiences of participating in the intervention and their use of the different program functions. The interviews will be digitally recorded, transcribed verbatim and will be analyzed using qualitative content analysis.^[62]^

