#### Fex-Can Childhood RCT

2.16.2

All data analyses will be performed and reported in line with the SPIRIT-PRO Extension for randomized clinical trials.^[64]^ The statistical analyses will primarily aim at comparing the intervention with the control group directly after end of program. The 3-month follow-up assessment will be used as secondary end-point comparing the intervention group and the control group. In addition, sustainment of a potential effect for the intervention group at 6 months (long-term assessment) will be evaluated. Missing data will be investigated using descriptive statistics and significance testing. Intention-to-treat analyses will be applied for the primary outcomes in the RCT.

All statistical analyses will be conducted by external statisticians, who are not aware of the study participants’ group allocation. SPSS Statistics version 26 (IBM Corp., Armonk, NY) will be used for data management and statistical analyses.

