### Adverse effects

2.17

In order to assess adverse effects for participants in the Fex-Can Childhood RCT, the number of participants reporting possible worsening of symptoms in the primary or secondary outcomes will be evaluated. Furthermore, participants will be asked to specify in the post-intervention survey if they have experienced any worsening of symptoms. Additionally, during the semi-structured post-intervention interview, participants will be asked to describe possible adverse effects experienced.

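### Self-reported worsening is described for the intervention arm only, so it has no control rate, although an untreated wait-list arm is surveyed at the same times

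*Protocol article*

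**What the plan says.** Section 2.17 of the protocol article (Adverse effects) draws on three sources.

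- **Scores:** "the number of participants reporting possible worsening of symptoms in the primary or secondary outcomes will be evaluated". No size of worsening, time point or comparison between arms is given.
- **Survey question:** "participants will be asked to specify in the post-intervention survey if they have experienced any worsening of symptoms". No arm is named.
- **Interview:** participants describe adverse effects they experienced. Section 2.11.2 defines who is interviewed: "Semi-structured interviews will be conducted with a purposive sample of ∼30 participants in the intervention group".

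Section 2.11.1 describes the process-evaluation part of the post-intervention survey. It covers adherence, use of program features and "perception of change in sexual problems and/or fertility-related distress". On recipients it says: "These questions will be administered to the participants belonging to the intervention group and will encompass 13 study-specific items". It then adds a 7-point item, from much improved to much worsened, on which people rate their present problems "in comparison to the level before they entered the Fex-Can Childhood intervention".

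On the comparator, section 2.1 says: "The control group will receive access to the intervention after the 3-month follow-up assessment". Section 2.16.2 says: "The statistical analyses will primarily aim at comparing the intervention with the control group directly after end of program", with the 3-month assessment as a secondary between-arm endpoint.

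**The concern.** A program that asks people to face sexual or fertility problems might increase distress in some of them. That is a hypothesis of this review and not a claim of the protocol, but section 2.17 exists to look for such effects. A worsening rate from treated people alone mixes any program effect with two other things.

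- **Natural fluctuation** makes some people worse over 12 weeks whatever they receive.
- **Regression to the mean** pulls the other way. Section 2.3.2 admits people because they score beyond a cut-off, and section 2.2.2 uses that same survey as baseline. Some will drift back towards the average untreated, which can hide harm in an uncontrolled rate.

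A concurrent randomized control removes both. The trial has one, but the self-report items as described do not use it. An analysis plan could later supply a threshold or a table by arm. It cannot supply answers that were never collected from the wait-list arm. Section 3 foresees implementation in routine care if the program proves efficacious, and the harm evidence would then be read alongside the efficacy result.

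**Working it through.** **1. Who supplies which harm data**

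| Source | Arm, as described | Untreated control rate? |
|---|---|---|
| Perceived-change items (2.11.1) | Intervention only, stated | No |
| 7-point change item (2.11.1) | Intervention, from context and from an anchor that does not fit untreated people | No |
| Worsening question (2.17) | Not named; intervention only if it belongs to the 2.11.1 items | Unclear |
| Interviews (2.11.2) | About 30 from the intervention arm, purposive | No |
| Outcome scores (2.16.2, 2.17) | Both arms | Available, but no between-arm use stated for harm |

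Section 2.2.2 has wait-list participants complete a post-intervention assessment after their own later access. Even if the change items were included then, those answers would come from treated people at a later time, so they would not be a control rate.

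**2. The plan's own figure**

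Section 2.13 asks for 128 completers per program (effect size 0.5, power 80%, α = 0.05). A two-sided two-sample t-test needs 63.8 per arm, so 64 per arm and 128 in total, which reproduces the figure. The article states no figure for harms.

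**3. How much worsening to expect with no program effect**

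Assumptions, not in the documents: standardized normal scores and retest correlation r of 0.6, 0.7 or 0.8. Worsening is set at 0.5 SD for illustration.

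*Unselected people.* SD of change = √(2(1 − r)); P(worse by ≥ 0.5 SD) = 1 − Φ(0.5 / SD).

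- r = 0.6: SD 0.894, P = 0.288
- r = 0.7: SD 0.775, P = 0.259
- r = 0.8: SD 0.632, P = 0.215

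*People starting exactly at a cut-off 0.5 SD worse than the mean* (the size in 2.3.2 for sexual function, assuming that survivors regress to that same mean). Expected drift back = 0.5(1 − r); residual SD = √(1 − r²).

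- P(worse by ≥ 0.5 SD) = 1 − Φ((0.5 + drift) / residual SD)
- P(better by ≥ 0.5 SD) = 1 − Φ((0.5 − drift) / residual SD)

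| r | Drift (SD) | Residual SD | Worse | Better |
|---|---|---|---|---|
| 0.6 | 0.20 | 0.800 | 0.191 | 0.354 |
| 0.7 | 0.15 | 0.714 | 0.181 | 0.312 |
| 0.8 | 0.10 | 0.600 | 0.159 | 0.252 |

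Without any effect, improvers outnumber worseners at every r shown, and the worsening rate depends on unknown quantities. A treated-only rate of 20%, say, could not be interpreted. The 7-point item is a rating and not a score, so this shows the mechanism and does not predict its distribution.

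**4. If the score-based count meant decline on any score**

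Simulated with equally correlated changes, no true effect, 10 to 22 scores per person, r from 0.5 to 0.8 and correlation between changes from 0 to 0.5 (all assumed):

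- any decline at all: about 91% to 100% of participants
- decline of at least 0.5 SD on some score: about 64% to 100%

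If the program worsened every score by 0.2 SD, comparing arms on any decline would have about 3% to 20% power at 64 per arm, where power could be computed. These figures apply only to the any-score reading.

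**5. What a comparison by arm could show**

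At 64 per arm, 80% power and two-sided α = 0.05, the detectable contrast is 10% versus about 30%, or 20% versus about 43%. With 25% worsening in both arms, the 95% interval for the risk difference has half-width 1.96 × √(2 × 0.25 × 0.75 / 64) = 0.150, or 15 percentage points.

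**The case against.** The best defence is that the trial does hold controlled harm data. A reader might infer from 2.11.1 and 2.17 that no planned measure can show whether the program harms people. The documents do not support that. The score-based count concerns RCT participants without limit to one arm, the outcomes are collected in both arms, controls stay untreated through 3 months, and average worsening on a primary outcome would appear in the planned comparison.

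A reader might also infer that nearly every participant will be counted as harmed. That needs the any-score reading. Section 2.17 can equally mean a count per outcome, and it speaks of symptoms, which fertility knowledge and self-efficacy are not.

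Third, the restriction to the intervention group is stated for process-evaluation items, most of which make no sense for people without access. The worsening question in 2.17 names no arm, so its restriction is an inference. Fourth, a threshold, a time point and a table by arm are commonly left to an analysis plan or full protocol, which are not shown here.

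All four stand and limit the point. They do not answer the rest of it: the perceived-change items and interviews are described for the intervention arm, the 7-point anchor does not fit untreated people, and the two sections leave open who answers the worsening question. Those are matters of data collection, which an analysis plan cannot repair.

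**Conclusion.** The point holds in a limited form. As described, perceived change and the interviews have no wait-list counterpart, so self-reported worsening cannot be separated from natural fluctuation or regression to the mean. For the worsening question in 2.17, the arm is unclear. The score-based count can be compared between randomized arms, but the article states no such comparison; its lack of a threshold is not itself held against the plan.

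The part that rests on the text needs no assumption. The sizes do: 16% to 29% worsening by 0.5 SD on one score without any effect, depending on r and on selection, under normality. The 91% to 100% figure depends on a reading that the text does not require and is not part of the conclusion. The efficacy analysis is unaffected. This is a cheap improvement.

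**What to change.** 1. Reconcile 2.11.1 with 2.17: state which arm answers the worsening question and whether it belongs to the 13 items.
2. Put the 7-point change item and the worsening question to both arms at post-intervention, and again at 3 months while controls are still untreated. Use a neutral anchor, such as *compared with when you joined the study*. Items on adherence and program features stay with the intervention arm.
3. Predefine worsening on each program's primary outcome (Satisfaction with sex life; overall RCAC mean). A change of 0.5 SD would serve as an example, but it is an assumed cut-off with no basis in the documents. State that the score-based count is made per outcome.
4. Report the self-report items and this criterion by arm, with the risk difference and 95% confidence interval, separately for each program.

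**Cost:** one or two extra items for the wait-list arm and one extra table. **Limit:** at 64 per arm only large differences are detectable, so the interval should be presented as descriptive, and a null result should not be read as evidence of safety.

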#### Semi-structured interview

2.11.2

Semi-structured interviews will be conducted with a purposive sample of ∼30 participants in the intervention group in order to achieve a deeper understanding of the intervention usage, and the role of the program in bringing about a change in the outcomes. The interviews will be performed via telephone, shortly after completion of the intervention. Questions will explore the participants’ view of their sexual problems or fertility-related distress and if/how these problems have changed during the course of the intervention. Participants will also be asked to describe their experiences of participating in the intervention and their use of the different program functions. The interviews will be digitally recorded, transcribed verbatim and will be analyzed using qualitative content analysis.^[62]^

### Participant timeline

2.12

See Table 1 for study timeline.

### Sample size

2.13

All eligible individuals registered in the National Quality Registry for Childhood Cancer and matching the inclusion criteria for the Fex-Can Childhood OS-study (∼4500) will be approached and invited to participate. With an estimated response rate of 60% the sample size (n = 2700) will be large enough to analyze clinical and sociodemographic predictors of the sexual dysfunction and fertility-related distress. With regards to the Fex-Can RCT we expect ∼50% of the participants in the Fex-Can OS study to rate high levels of sexual problems or fertility-related distress (n = 1350). These individuals will be invited to participate in the RCT. In order to detect a statistically significant group difference with a power of 80%, estimating medium effect size (0.5) and α = 0.05, a total of 128 completers (post-intervention assessment) will be required in each version of the program in the RCT. We expect ∼30% of the individuals who are invited to the RCT to agree to participate (n = 405). With an estimated attrition rate of 15% at the post-intervention assessment we will reach well over 256 completers and achieve adequate statistical power in the Fex-Can RCT.

### Randomization

2.14

Participants will be randomly assigned to either intervention-group or wait-list control-group with an allocation ratio of 1:1. Participants will be allocated in blocks stratified by sex and diagnosis (leukemia/lymphoma; brain tumor; solid tumor). The randomization will be carried out separately for the two programs of the RCT (Fex-Can Childhood Sex and Fex-Can Childhood Fertility). In the event that participants’ eligibility criteria are met for both programs, an evaluation of individual scores will be performed based on severity of reported problems by a registered psychologist and a registered nurse specialized in psychosocial oncology.

In order to minimize bias, the computer-generated randomization sequence will be created by a statistician not directly involved in the management of the trial and the information regarding the series of random numbers will be kept unknown to the investigators.

### Blinding

2.15

Due to the nature of the intervention, it is not possible to conceal the participants’ group allocation to the researchers involved in providing and monitoring the intervention and data collection. Hence, full blinding is infeasible during the intervention in the present study, however, participants’ allocation to intervention or control groups will be masked in the data set available for researchers during data analysis.

### Statistical methods

2.16

#### Fex-Can Childhood OS

2.16.1

All data analyses will be performed and reported in accordance with STROBE^[63]^ for observational studies. With the exception of descriptive statistics and visualizations, multiple regression models will be the main class of statistical method used to analyze prevalence and predictors of the outcomes. Missing data will be investigated using descriptive statistics and significance testing.

#### Fex-Can Childhood RCT

2.16.2

All data analyses will be performed and reported in line with the SPIRIT-PRO Extension for randomized clinical trials.^[64]^ The statistical analyses will primarily aim at comparing the intervention with the control group directly after end of program. The 3-month follow-up assessment will be used as secondary end-point comparing the intervention group and the control group. In addition, sustainment of a potential effect for the intervention group at 6 months (long-term assessment) will be evaluated. Missing data will be investigated using descriptive statistics and significance testing. Intention-to-treat analyses will be applied for the primary outcomes in the RCT.

All statistical analyses will be conducted by external statisticians, who are not aware of the study participants’ group allocation. SPSS Statistics version 26 (IBM Corp., Armonk, NY) will be used for data management and statistical analyses.

### Adverse effects

2.17

In order to assess adverse effects for participants in the Fex-Can Childhood RCT, the number of participants reporting possible worsening of symptoms in the primary or secondary outcomes will be evaluated. Furthermore, participants will be asked to specify in the post-intervention survey if they have experienced any worsening of symptoms. Additionally, during the semi-structured post-intervention interview, participants will be asked to describe possible adverse effects experienced.

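### Participants are asked directly about experienced worsening only around the end of the program, although surveys also go out at 3 and 6 months

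*Protocol article*

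**What the plan says.** Section 2.17 of the protocol article gives three routes for detecting harm in the RCT.

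1. **Outcome scores:** "the number of participants reporting possible worsening of symptoms in the primary or secondary outcomes will be evaluated". No time point is attached to this count.
2. **Direct question:** "participants will be asked to specify in the post-intervention survey if they have experienced any worsening of symptoms".
3. **Interview:** "during the semi-structured post-intervention interview, participants will be asked to describe possible adverse effects experienced".

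Other sections fill in who is covered and when.

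- Section 2.11.2 on the interviews: "Semi-structured interviews will be conducted with a purposive sample of ∼30 participants in the intervention group". On timing: "The interviews will be performed via telephone, shortly after completion of the intervention".
- Section 2.11.1 on the process items in the post-intervention survey: "These questions will be administered to the participants belonging to the intervention group and will encompass 13 study-specific items". The same survey holds a perceived-change rating: "Responses will be given on a 7-point scale, ranging from “Much improved” to “Much worsened” with the midpoint “No change".
- Sections 2.2.2 and 2.9 place the outcome assessments at end of program, 3 months and 6 months, with the same instruments in the same order each time. The battery listed in 2.9 contains no question on experienced worsening.
- Section 2.13 plans "With an estimated attrition rate of 15% at the post-intervention assessment".

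**The concern.** The direct question and the outcome scores give different information. A score shows that a participant's sexual function, reproductive concerns or mood has changed. The direct question shows whether the participant has experienced worsening, including worsening that the chosen scales do not register. The article describes the direct question, the perceived-change rating and the interview once each, all around week 12, while the study goes on surveying the intervention group for another six months.

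Two groups are then not asked directly: those who miss the post-intervention survey but answer a later one, and those who notice worsening only after the 12 weeks. The content concerns sexuality and threatened fertility, so some participants may find it upsetting, and non-response to the first survey may not be unrelated to that. The discussion section says that steps will be taken to implement the program in routine care if it proves efficacious. The account of perceived harm at that stage would come from one time point and from those who answered then.

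**Working it through.** **Inputs, all from the protocol article.** 4500 people approached, 60% response, 50% with high levels of problems, 30% agreeing to the RCT, 15% attrition at the post-intervention assessment, and 128 completers needed per program (2.13). Allocation is 1:1 (2.14). About 30 interviews are planned (2.11.2).

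**The plan's own figures.**
- For 80% power, effect size 0.5 and two-sided alpha 0.05 (sidedness is not stated, so this is assumed), an exact two-sample t-test needs 63.77, so 64 per arm and 2 × 64 = 128 per program. The stated figure reproduces.
- 4500 × 0.60 = 2700; 2700 × 0.50 = 1350; 1350 × 0.30 = 405. This also reproduces.
- 405 × 0.85 = 344, above the 256 needed for both programs.

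The sample size is not in dispute. These figures only give the scale.

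**How many do not answer the direct question when it is put.** Assume the 15% applies equally in both arms.
- Intervention participants across both programs: 405 / 2 = 202.5, about 202.
- Not returning the post-intervention survey: 202.5 × 0.15 = 30.4, about 30.
- Returning it: 202.5 × 0.85 = 172.1, about 172.
- If recruitment only just met the requirement: 256 / 0.85 = 301.2, so 302 randomised; 302 / 2 = 151; 151 × 0.15 = 22.7, about 23 not answering.

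**How many of these a repeated question could reach.** The article does not say how many non-responders at end of program answer later. The number lies between 0 (all have left the study) and about 30 (all answer at 3 or 6 months). A repeated item would also reach those of the 172 responders who perceive worsening later; their number cannot be derived from the document.

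**Interview coverage.** 30 / 202.5 = 14.8% of intervention participants, chosen purposively and interviewed close to the end of the program.

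**Illustration of non-response, with assumed rates.** Suppose 5% of responders report worsening, and 10%, 20% or 40% of non-responders would have done so. The rate over everyone is 0.85 × 5% + 0.15 × 10% = 5.75%, or 7.25% at 20%, or 10.25% at 40%, against a reported 5%. None of these rates is in the protocol. They show how the gap behaves, not how large it is.

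**Which route operates when, as described.**

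| Route | End of program | 3 months | 6 months |
|---|---|---|---|
| Outcome instruments given | yes | yes | yes |
| Score-based worsening count | time points not stated | time points not stated | time points not stated |
| Direct question on worsening | yes | not described | not described |
| Interview (about 30) | yes, shortly after | no | no |

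**The case against.** The strongest reply is that later worsening is already covered. A reader who looks only at the direct question might infer that anyone who deteriorates after week 12 is missed altogether, or that benefit is followed for about nine months while harm is looked for once. The document does not support that. The first route in 2.17 counts worsening in the primary and secondary outcomes, those instruments are repeated at every assessment, and scores can move in either direction. Up to 3 months they also have a randomised comparator, which a self-report of worsening in one arm lacks. This objection stands, and it limits the point to direct self-report.

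Two further inferences fail.
- A reader might take everyone who stops because they feel worse to be lost. Section 2.13 defines completers by the post-intervention assessment, and 2.11.1 addresses its items to the intervention group without requiring that modules be finished. Someone who stops using the program can still be sent the survey and answer it. Only non-responders to the survey are lost to the question.
- A reader might take the interviews to be restricted to people who finished the modules. The wording in 2.11.2 gives timing after a 12-week program. It sets no eligibility rule, and purposive selection could include low users.

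It can also be said that this is a condensed article, that Table 1 is not shown, and that follow-up survey items may be set out in a fuller document. That lowers confidence but does not remove the point. Section 2.17 names the survey in which the question is placed. Where the article means an item to be in the follow-up assessments too, it says so, as 2.4.2 does for use of concomitant care.

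**Conclusion.** The point holds in a limited form and is minor. As described, the direct question on experienced worsening is put once, at end of program, with about 30 purposive interviews around the same time. About 30 of about 202 intervention participants would not answer it then, given 405 randomised 1:1 and 15% attrition that is equal by arm; the figure is about 23 of 151 if recruitment only just meets the requirement. Those among them who answer a later survey, and those who first perceive worsening after week 12, are not asked directly.

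Later worsening is not invisible, because the outcome scores at 3 and 6 months can show it. The article does not say, however, that the score-based count is made at those time points. The size of any bias in the reported rate of perceived worsening cannot be worked out from the document.

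**What to change.** Repeat the same worsening item in the 3-month and 6-month surveys of the intervention group, worded as *since the last questionnaire you answered*, so that someone who skipped the end-of-program survey reports on the whole interval. State in section 2.17 that the score-based worsening count is also made at 3 and 6 months. At 3 months it can be compared with the wait-list group. At 6 months it describes the intervention group only, since by then the controls have been given access.

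The cost is one extra item in two surveys that are already being sent, and no new assessments. The change does not reach people who leave the study entirely, and the report should say so.
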